### Sample size

The primary outcome measure of the study is reoperation rates, and the sample size is based on this metric. Reoperation rates are assumed to be 13% for CF and 27% for TBW, based on a previous study at our institution [16]. As active patient participation is not required to calculate reoperation rates, and as it will be collected in the same health-care system as the previous retrospective study, we do not expect any drop-out of participants (relative to that study) for assessment of reoperations. The sample size of each arm needed to achieve 80% power is 98; thus, we plan to recruit a total of 200 participants, yielding 81% power.

We expect all 200 participants to be available for analyses of peri-operatively recorded variables (age, sex, fracture type, fluoroscopy DAP, fluoroscopy time and operation time). For analyses of complications, the same assumption is made as for reoperations, i.e. no drop-out relative to our previous retrospective study. For all other variables collected at follow-up, we expect 170 participants to be available for statistical analysis. The expected power for all variables at different sample sizes are shown in Table 1, including all relevant assumptions made.

**Table 1 Tab1:** Statistical power and sample size requirements for study outcomes

	**Power *****n***** = 200**	**Power *****n***** = 170**	***n***** needed for 80% power**	**MDD *****n***** = 100**	**MDD**	**MDD *****n***** = 170**	**MDD**	**x̄ or proportion**	**SD**	**MCID**

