### Post-inclusion withdrawals and exclusions

Participants included during the initial assessment may be excluded at any point post-inclusion if exclusion criteria are met. If consent has been given at this point, the data already recorded will be analysed. Participants may decide to voluntarily withdraw at any point, receiving standard healthcare. Upon withdrawal, participants may choose to allow previously and future health-care data to be analysed, only allow previously collected data to be analysed, or decline analysis of any such data.

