### Statistical analysis

For power and sample size calculations, the alpha value was set to 0.05. Our hypothesis is that CF will yield lower reoperation and complication rates, lower intra-operative radiation, and less intra-operative fluoroscopy time; thus, one-sided tests of proportions were used for sample size requirements calculations [47]. For all other variables, tests for non-inferiority were used with assumed means for ratio scalar and interval variables and assumed proportions for nominal variables [47].

Statistical power and sample size requirements for demonstrating clinically significant differences between the groups were calculated using minimal clinically important difference (MCID) values from the literature. Power and sample size data, including relevant assumptions for all calculations, are presented in Table 1.

We expect ≥ 80% power for reoperation rates, complication rates, severe complication rates, *Quick*DASH, SMFA, patient satisfaction, pain in motion and at rest, and ROM. However, we do not expect to achieve 80% power for analysis of grip strength, postoperative antibiotics use, secondary dislocation or nonunion rate, sick-leave time, fluoroscopy time, fluoroscopy DAP, or operation time (Table 1).

The minimal detectable differences (MDD) for various outcomes and study sizes are presented in Table 1. For some of the secondary and tertiary outcome measures, the MDD is smaller than the MCID meaning that the study is under-powered for proving non-inferiority between the groups. Early termination of the trial resulting in a smaller sample size would further reduce MDD, hampering the power of the study.

The final study groups consist of all participants that complete the follow-up and participants that withdraw but permit analysis; see the section “ Post-inclusion withdrawals and exclusions”. The study groups will be compared using the chi-squared test for categorical variables (reoperation, complication) and Student’s *t*-test for continuous variables.

Comparisons between the study groups will primarily be performed by “intention to treat” analyses. If large cross-over between study groups occurs, “as treated” analyses will be performed as well. Subgroup analysis stratified by Mayo classification, age, gender, open fracture, and high energy trauma is planned for all outcomes.

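### Participants with truncated follow-up can only count as free of reoperation in the primary chi-squared test; the likely effect is small, and censoring would handle it

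*Protocol article*

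**What the plan says.** Table 1 of the article gives the primary outcome as reoperation, yes or no. The Statistical analysis section names the test: "The study groups will be compared using the chi-squared test for categorical variables (reoperation, complication" and so on. It builds the groups from people who complete follow-up and "participants that withdraw but permit analysis", and refers to the section on post-inclusion withdrawals and exclusions.

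That section gives a withdrawing participant three choices:
- release past and future health-care data;
- "only allow previously collected data to be analysed";
- release nothing.

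It also lets participants be excluded at any time after inclusion. If they had consented, what was recorded up to then is analysed.

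Follow-up ends at 36 months. Reoperations are taken from medical records at the interim analyses and at the end of the trial. The Sample size section expects no drop-out for this outcome relative to the earlier retrospective study.

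**The concern.** Two kinds of participant can be in the analysis with less than 36 months of observation: withdrawers who release past data only, and consented participants excluded after inclusion. A 2x2 table has no cell for partial follow-up. A member of either class who leaves at month 2 without a reoperation is therefore counted with those who were observed event-free to month 36.

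This follows from the stated set combined with the stated test. It lowers the crude reoperation rate in each arm according to how many leave early and how many of their reoperations fall after exit. Equal exit in the arms shrinks the absolute difference. Unequal exit could move it either way. The comparison concerned is the one that sizes the trial.

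**Working it through.** **Inputs from the article.** "Reoperation rates are assumed to be 13% for CF and 27% for TBW" (Sample size); "the alpha value was set to 0.05" and "one-sided tests of proportions were used for sample size requirements calculations" (Statistical analysis); 1:1 allocation; 200 participants, so n = 100 per arm.

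**Reproducing the planned figures.** The article states "The sample size of each arm needed to achieve 80% power is 98" and "we plan to recruit a total of 200 participants, yielding 81% power". With a one-sided z-test and unpooled variance:

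n = (1.645 + 0.842)² × (0.13×0.87 + 0.27×0.73) / 0.14² = 97.85, so 98 per arm.

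Power is 80.8% at 100 per arm and 74.9% at 85 per arm, which matches the stated 81% and 75%. The pooled form is used below because it corresponds to the chi-squared test:

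power = Φ[(d − 1.645·√(2p̄(1−p̄)/n)) / √((p₁q₁ + p₂q₂)/n)]

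With d = 0.14 and p̄ = 0.20 this is Φ[(0.14 − 1.645×0.05657)/0.05570] = 80.0%. That is the reference.

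**Effect of truncation.** Let w be the share of an arm with truncated follow-up and f the share of their reoperations that occur before exit. Scoring the rest as non-events gives

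observed rate = true rate × (1 − w(1 − f)).

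The documents give neither w nor f, so both are assumed. For f = 0.5:

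| Truncated, CF / TBW | CF rate | TBW rate | Difference (points) | One-sided power |
|---|---|---|---|---|
| none | 13.000% | 27.000% | 14.00 | 80.0% |
| 2% / 2% | 12.870% | 26.730% | 13.86 | 79.6% |
| 5% / 5% | 12.675% | 26.325% | 13.65 | 78.9% |
| 10% / 10% | 12.350% | 25.650% | 13.30 | 77.7% |
| 15% / 15% | 12.025% | 24.975% | 12.95 | 76.5% |
| 5% / 15% | 12.675% | 24.975% | 12.30 | 72.2% |
| 15% / 5% | 12.025% | 26.325% | 14.30 | 82.6% |

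Example, third row: 0.13 × (1 − 0.05×0.5) = 0.12675; 0.27 × 0.975 = 0.26325; difference 0.1365.

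The 15% value is an outer bound. It is the loss the Sample size section expects for outcomes that need attendance (170 of 200 available). With 15% in both arms and no event seen before exit (f = 0), the difference is 11.9 points and power 72.7%. Under equal truncation the risk ratio stays at 0.13/0.27 = 0.481.

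**Type I error.** Assume 20% in both arms and f = 0.5. Equal truncation leaves it at 5.0%. In a two-sided test, 5% against 15% gives about 5.4%, and 0% against 15% about 5.8%. In a one-sided test for CF, 15% CF against 5% TBW gives 7.15%, and the reverse gives 3.4%.

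**The case against.** The strongest case against is that the outcome barely depends on participation. Reoperations come from medical records. The hospital is the only one treating these fractures in its catchment area, and residents of other health-care regions are excluded. A missed visit truncates nothing; a withdrawer must refuse use of future records. Nor does the article say that unseen months are coded as event-free, and handling of incomplete follow-up is often left to an analysis plan.

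Much of this stands. It rules out the broader reading that withdrawers in general enter with short follow-up: those who permit future data are followed through records, and those who refuse everything are not analysed. It also makes a small w likely.

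It does not remove the point. The article fixes both the set and the test, and together they leave a truncated participant without an event only one cell. The drop-out expectation is relative to the earlier study, and the Discussion allows for reoperation data lost when people move away. It also notes that the earlier study enrolled only elderly patients. Post-inclusion exclusions add to the truncated group, since the criteria include dementia and living in another health-care region, either of which could arise during follow-up.

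A further objection is that censoring assumes exit is unrelated to reoperation risk. That is true, but scoring truncated people as non-events assumes no reoperation at all after exit, which is the stronger assumption.

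**Conclusion.** The point holds for past-data-only withdrawers and for consented participants excluded after inclusion. With half of their reoperations unseen, equal truncation of 2-10% shrinks the 14-point difference by 0.14 to 0.70 points and costs 0.4 to 2.3 points of one-sided power. Risk ratio and type I error are unchanged. If few leave, the effect is close to nil.

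A reader might infer that the primary comparison is distorted, or could be turned in favour of one arm. The documents do not support that. A shift in either direction needs truncation that differs between arms. The Blinding section lets participants learn their method on request, which makes such a difference possible, but nothing shows that it would lead one arm to refuse record access more often. The 12.3- and 14.3-point results show sensitivity to that assumption and are not forecasts.

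The figures take 36 months, the end of follow-up, as the horizon of the primary comparison, and rest on the assumed w and f.

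**What to change.** Estimate the 36-month cumulative incidence of first reoperation in each arm by Kaplan-Meier, or by Aalen-Johansen with death as a competing event. Censor at the last date covered by permission to use records or, for participants excluded after inclusion, by recorded data. Report the 36-month risk difference with its 95% confidence interval as the primary result, and keep the chi-squared test as a sensitivity analysis. State the assumption of non-informative censoring and check it with a simple sensitivity analysis, for example by varying the reoperation risk after exit by arm. Report the number truncated in each arm.

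The cost is wording and a little more analysis work. Reoperations are already being retrieved from medical records, so their dates should be available there. If nobody is truncated, the Kaplan-Meier difference equals the crude difference, so the proportion-based sample size still applies. The change should be made before the comparative data are examined.

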The controversy over treatment method for Mayo 2a and 2b fractures elicits the need to examine our research question: Is outcome following CF better than TBW for Mayo type 2a and 2b olecranon fractures? Our hypotheses are that CF will result in lower reoperation rate, complication rate, and intra-operative radiation time and exposure compared with TBW, while yielding non-inferior results in our specified secondary and tertiary outcome measures, including the patient related outcome *Quick*DASH. We aim to investigate this in a prospective 1:1 randomized controlled trial (RCT).

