**Tertiary measures**										
ROM, flexion (degrees)	> 99%	> 99%	18	4.1	3.3	3.1	2.9	146^h^	7^h^	10^b^
ROM, extension (degrees)	> 99%	> 99%	10	2.9	2.4	2.2	2.1	− 3^h^	5^h^	10^b^
ROM, supination (degrees)	> 99%	> 99%	14	3.5	2.9	2.7	2.5	80^h^	6^h^	10^b^
ROM, pronation (degrees)	> 99%	> 99%	18	4.1	3.3	3.1	2.9	87^h^	7^h^	10^b^
Grip strength (newton)	43%	31%	352	9.4	7.6	7.2	6.6	32^i^	16^i^	5 ^j^
Post-operative antibiotics (yes/no)	< 1%	< 1%	6296	16%	13%	12%	11%	8%^a^	-	2%^b^
Secondary nonunion (yes/no)	< 1%	< 1%	9782	< 0.1%	< 0.1%	< 0.1%	< 0.1%	1%^k^	-	0.5%^b^
Sick leave (days)	< 1%^n^	< 1%^l^	30,790	18	14	13	12	35^b^	302	12
Fluoroscopy time (seconds)	< 1%	< 1%	3024	55	45	42	39	81^m^	94^m^	10^b^
Fluoroscopy DAP (mGy·cm^2^)	< 1%	< 1%	1492	19	16	15	14	25^m^	33^m^	5^b^
Operation time (minutes)	< 1%	< 1%	998	15	13	12	11	83^m^	27^m^	5^b^

Calculations of power and sample size requirements (n) for all outcome measures, including underlying assumptions. Previously published Minimally Clinically Important Differences (MCID) are given for outcomes where non-inferiority testing is performed and are used as non-inferiority margins in statistical analyses

^a^Based on a previous study at our institution [16]

^b^Based on estimations by the authors

^c^Based on QuickDASH following TBW [31]

^d^Based on unpublished data from a previous study where standard deviation (SD) was 22 for CF and TBW, although the sample was small

^e^Ranging from 3.5 to 19 points in the literature with a mean of 14 points [32–36]

^f^Based on outcomes following distal radius fractures as no elbow specific data was found in the literature [37]

^g^To our knowledge, no studies have reported MCID of SMFA following surgery for upper extremity injuries. The MCID was estimated to be half the standard deviation [38]

^h^Based on normal ROM [39]

^i^Based on data on elbow fractures [40]

^j^Based on a review of MCID of grip strength [41]

^k^Based on a study on the outcome of 196 olecranon fractures [42]

^l^Power if *n* = 100 and *n* = 85 as we expect half of the participant to work

^m^Based on data from all CF and TBW cases at our department during 2020

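### Non-inferiority outcomes rest on intention to treat, with an as-treated check only if cross-over is judged large, although cross-over itself favours a non-inferiority conclusion

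*Protocol article*

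**What the plan says.** The Introduction hypothesises that CF will lower reoperations, complications and intra-operative radiation "while yielding non-inferior results in our specified secondary and tertiary outcome measures", with QuickDASH named among them. The Null hypothesis section repeats this split between superiority and non-inferiority outcomes.

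Non-inferiority is more than a sample-size device. The note to Table 1 says that the listed minimal clinically important differences "are used as non-inferiority margins in statistical analyses". The Statistical analysis section expects at least 80% power for QuickDASH, SMFA, satisfaction, pain and range of motion.

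The same section then gives one rule for all outcomes: "Comparisons between the study groups will primarily be performed by" intention to treat. An as-treated analysis follows only "If large cross-over between study groups occurs". The article does not say how much cross-over counts as large or who decides. It makes no distinction between superiority and non-inferiority outcomes, and does not ask for two analyses to agree before non-inferiority is claimed.

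**The concern.** In a superiority comparison, a patient who receives the other arm's operation dilutes the difference and makes a positive claim harder. Intention to treat is then conservative, which suits reoperations and complications. In a non-inferiority comparison the same dilution moves the estimate towards zero and away from the margin, so a positive claim becomes easier.

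The plan treats both kinds of outcome alike and makes its only check depend on an undefined trigger. With some cross-over that nobody calls large, the trial could report CF as no worse on function and pain partly because the arms were mixed, and the printed plan would not require a second analysis that might show it.

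**Working it through.** **Inputs**
- Alpha: "For power and sample size calculations, the alpha value was set to 0.05". For the superiority outcomes, "one-sided tests of proportions were used for sample size requirements calculations". For the rest, "For all other variables, tests for non-inferiority were used". The level of the final non-inferiority test is not stated; one-sided 5% is assumed, and 2.5% is also shown.
- Numbers: 170 participants expected for follow-up variables (Sample size), so 85 per arm at 1:1.
- QuickDASH: margin 14, SD 22 (Table 1). The margin's footnote reads "Ranging from 3.5 to 19 points in the literature with a mean of 14 points".
- SMFA: margin 9, SD 18. Pain: margin 1, SD 2. Both margins are 0.5 SD.
- Cross-over rate: none given, so a range is used.

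**The plan's own figure first.** Primary outcome, 13% v 27%, one-sided 5%, 80% power, unpooled variance:

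n per arm = (1.645 + 0.842)² × (0.13×0.87 + 0.27×0.73) / 0.14² = 97.8, so 98, as printed. At 100 per arm the power is 80.8%, printed as 81%. This confirms the one-sided 5% reading for the primary outcome.

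**Formula.** Let proportions a and b of the two arms receive the other operation, and let c = a + b be the net cross-over. If each such patient takes on the full effect of the operation received, and crossing over is unrelated to prognosis, the expected intention-to-treat difference is (1 − c) × true difference. Non-inferiority is declared when the estimate lies below margin − z × SE. With the true difference at the margin:

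false non-inferiority rate = Φ(c × margin/SE − z), where SE = SD × √(2/85).

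- QuickDASH: SE = 22 × 0.1534 = 3.37; margin/SE = 4.15.
- SMFA: SE = 18 × 0.1534 = 2.76; margin/SE = 3.26. Pain has the same ratio.

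Example, QuickDASH at c = 0.10: Φ(0.415 − 1.645) = Φ(−1.230) = 10.9%.

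| Net cross-over | Equivalent to | QuickDASH | SMFA, pain |
|---|---|---|---|
| 0 | – | 5.0% | 5.0% |
| 5% | 2.5% of each arm | 7.5% | 6.9% |
| 10% | 5% of each arm, or 10% of one | 10.9% | 9.4% |
| 20% | 10% of each arm | 20.8% | 16.0% |

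In patients, net cross-over is c × 85: about 4, 8 to 9, and 17 of the 170.

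**Simulation check** (200,000 replicates, t-test against the margin): 10.9% and 9.3% at 5% of each arm; 20.1% and 15.9% at 10% of each arm.

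**Net cross-over that doubles the rate:** 8.8% for QuickDASH, 11.1% for SMFA and pain, 5.6% for satisfaction, 2.8% to 3.9% for range of motion, 17.8% for grip strength. The wider the margin in SD units, the greater the exposure.

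**Sensitivity**
- At one-sided 2.5%, 10% net cross-over gives 6.1% for QuickDASH and 5.1% for SMFA and pain, again at least double the nominal level.
- The QuickDASH sample size and power in Table 1 (138; 94%; 89%) fit a margin of 11 (0.5 SD) under a two-sided equivalence formula, not the printed 14. With a margin of 11, the QuickDASH results equal those for SMFA: 9.4% at 10% net and 16.0% at 20% net.

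**The case against.** **No cross-over rate is documented, and the design points to a low one.** There is a single operation, allocated just before the patient enters theatre, by surgeons familiar with both methods. This stands. A reader might infer that the trial's false non-inferiority rate is doubled. The article does not support that: doubling needs about 9–11% net cross-over for QuickDASH, SMFA and pain, and at 5% net the rate is only about 7–7.5%.

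**At 20% net the trigger might fire.** This also stands. The 16–21% figures may describe a case in which the as-treated analysis would be run, so it would be wrong to say that no check is planned.

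**The target may be the policy of allocating CF.** Intention to treat then keeps its nominal error and nothing is inflated. The article does not say which target it means, so the figures hold only for the effect of the operation received.

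**The true difference is set at the margin.** For QuickDASH that means CF is worse by 14 points, against an assumed mean of 13. This is demanding, but it is the boundary at which a non-inferiority test's error is defined.

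**Judging cross-over after seeing results is not stated.** A reader might infer it from the wording. The article says neither when nor by whom the judgement is made. The operation performed is known on the day of surgery, and analysis is to use a blinded data set.

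**A separate analysis plan could define large.** It could, and the missing threshold alone would be no finding. The weakness is the printed rule, which makes the check conditional for outcomes where dilution favours the claim.

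**A per-protocol set has its own bias.** If difficult fractures leave the CF arm, dropping them can itself favour CF. This stands and limits the remedy to a supplement.

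**Conclusion.** The concern holds in conditional form. For the non-inferiority outcomes, the plan relies on an analysis that cross-over biases towards the hoped-for conclusion, and its only check hangs on an undefined trigger.

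The size depends on a rate that the article does not give: a small inflation at 5% net cross-over, roughly a doubling at 10%, and a three- to fourfold rise at 20% for QuickDASH, SMFA and pain. This rests on the operation received as the target, a true difference at the margin, full transfer of effect in patients who cross over, 85 per arm and one-sided 5%.

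The primary outcome and the other superiority outcomes are not affected in this direction. The point bears on the secondary and tertiary claims only.

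**What to change.** For every non-inferiority outcome, drop the large-cross-over trigger. Always report the intention-to-treat analysis together with an analysis of participants who received their allocated fixation, and report the number of cross-overs and the reasons for them, by arm. Describe non-inferiority as established only when the two analyses agree, that is, when both confidence intervals exclude the margin. Keep intention to treat as primary for reoperations and complications.

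The cost is one extra analysis on data already held and a slightly lower chance of a non-inferiority claim. As an illustration, at a 0.5 SD margin, losing 5% of each arm (85 to about 81) lowers one-sided 5% power from Φ(3.26 − 1.645) = 95% to Φ(3.18 − 1.645) = 94%. The second set is not fully protected by randomisation, so it supplements intention to treat and does not replace it. The reasons for cross-over let readers judge whether it favours CF.

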### Ethics

The study was approved by the Swedish Ethical Review Authority (DNR: 2021–06822-01). The associated risks are primarily post- or peri-operative complications. As both interventions are standard care at our department, no additional such risk is implied by the trial. One additional risk is the potentially harmful effect of radiation received from the radiograph at 6 months, as this is not part of standard care. The additional effective radiation dose is estimated to 0.001 mSv and minimized by only using one projection. The more rigorous follow-up could potentially enhance rehabilitation and health for included participant compared to standard care. Future patients may benefit from improved future treatment recommendations based on study results. Using data from a previous study [16], the number needed to harm is estimated to 6.8 for reoperations and 3.1 for complications when TBW is chosen over CF. We believe that the potential benefits for study participants and future patients outweigh the additional risks for the participants in the study.

